# CanWalk: study protocol for a randomized feasibility trial of a walking intervention for people with recurrent or metastatic cancer

**DOI:** 10.1186/s40814-015-0003-5

**Published:** 2015-03-12

**Keywords:** Randomized controlled trial, Feasibility studies, Qualitative evaluation, Metastatic cancer, Recurrent cancer, Secondary cancer, Walking

## Abstract

**Background:**

Increasing numbers of people in the UK are living with recurrent or metastatic cancer, many of whom experience reduced quality of life resulting from the physical and psychosocial consequences of cancer and its treatment. While drug treatments are important at alleviating some symptoms, there is increasing evidence of the benefits of exercise in enhancing quality of life and health outcomes. Walking is an inexpensive and accessible form of exercise. To our knowledge, no studies have investigated whether a walking intervention is sufficient to enhance quality of life and alleviate symptoms in people with recurrent or metastatic cancer across a range of tumor types. This paper describes the CanWalk study protocol, which aims to assess the feasibility and acceptability of undertaking a randomized controlled trial of a community-based walking program to enhance quality of life and well-being in people with recurrent or metastatic cancer.

**Methods:**

A mixed methods feasibility study includes an exploratory two-center randomized controlled trial and qualitative interviews. A minimum of 60 participants will be recruited from two London NHS Trusts and randomized 1:1 between the walking intervention and standard care using minimization. The walking intervention consists of the initial provision of written/online information followed by a short motivational interview. Participants are instructed to walk for 30 min on alternate days and attend an organized volunteer-led walk once a week. Half of all participants will be asked to use a pedometer. Postal questionnaires will be completed at baseline (pre-randomization) and at 6, 12 and 24 weeks. A subsample of participants and stakeholders will be interviewed at the end of the study.

**Results:**

Primary outcomes will be the acceptability and feasibility of the intervention and trial. A range of secondary outcome assessments needed to design a main study, including estimates of recruitment, adherence and variability in quality of life, will be evaluated.

**Conclusions:**

Data from this study will be used to refine the walking intervention, investigate the acceptability of the intervention and study design, and determine the most appropriate outcome measures thereby providing estimates of the factors needed to design the main study.

**Trial registration:**

ISRCTN42072606.

## Background

Two million people are living with cancer in the UK today [1], and it is predicted that the number will increase to four million over the next 30 years [2]. The precise number of people living with recurrent cancer (the cancer has returned after treatment has ended) or metastatic cancer (the cancer has spread from the place where it first started) is unknown, although there is some evidence that the life expectancy of this group is also increasing [3]. Nevertheless, people with recurrent or metastatic cancer face a number of health challenges including psychological disorders [4] and physical symptoms, including pain, fatigue, and appetite loss [5]. While drug treatments are important at alleviating some of these symptoms, two recent systematic reviews identified the important potential contribution of exercise in enhancing the quality of life (QoL) in those with recurrent or metastatic cancer [6,7]. Specifically, programs that include regular walking for more than 30 min may generate improvements in QoL, physical functioning, and fatigue and are acceptable and well tolerated [6,8]. However, many of the interventions reviewed included different types of physical activity, were supervised, and required attendance at specialist exercise facilities, which may limit their acceptability or economic sustainability in the long term.

While many people with cancer may be hesitant to exercise [9], research from primary care demonstrates the effectiveness of brief advice, supported by written materials, at increasing physical activity levels [10]. Walking is an inexpensive form of exercise, it can be undertaken alone or in a group, and has demonstrated significant health benefits - including for cancer [11]. An additional advantage of walking is that it is not restricted to a specific facility or setting and has been shown to be associated with longer-term changes in behavior [10]. Preliminary results from a randomized pilot walking intervention in Sweden among men with prostate cancer suggest that regular group walking has positive effects on both quality of life and inflammatory and metabolic biomarkers [12]. However, no studies to date have investigated whether a walking intervention on its own is sufficient to enhance the physical and psychological well-being of people with recurrent or metastatic cancer across a range of tumor types.

Here, we describe the protocol of the CanWalk study, which aims to assess the feasibility and acceptability of undertaking a randomized controlled trial of a community-based walking program to enhance quality of life in people with recurrent or metastatic cancer. The study will promote a walking intervention, assess whether participants find it acceptable and evaluate whether a full randomized controlled trial is warranted and feasible. Specific objectives include:The development of the walking intervention to encourage intervention uptake [13];To investigate the acceptability to participants of a) the walking intervention, b) the study materials, and c) being randomized to intervention or control; and to assess d) the acceptability and timing of the selected outcome measures, and e) use of pedometers to enhance and measure adherence;To provide estimates of key aspects of trial design needed to design a full-scale randomized trial design, if warranted, including; a) number of eligible participants, b) recruitment rate, c) retention rate, d) response rates to initial and follow up questionnaires, e) the utility of objective and subjective methods to assess adherence to the walking intervention, and 4) generation of an estimate of the variability in quality of life.

## Methods

### Design

This is a mixed methods [14] feasibility study based on an exploratory two-center randomized controlled trial (RCT) with nested qualitative interviews. The study is registered with the International Standard Randomized Control Trial Number Register (ISRCTN42072606). Participants will be randomized, using a central online system, 1:1 between the walking intervention and standard care using minimization (based on age, sex, and physical activity levels).

### Setting and participants

The study will be undertaken in two large London NHS Foundation Trusts. Participants are eligible for the study if they i) are 16 years or over, ii) have a diagnosis of breast, colorectal, upper gastrointestinal, gynecological, hematological, head and neck, melanoma, or prostate cancer with recurrent or metastatic disease, iii) meet the eligibility criteria for specific cancer diagnoses (Table 1), and iv) are able to walk for a minimum of 30 min unaided. Exclusion criteria are i) having bone metastases which the responsible health-care professional considers a contraindication to participating in the walking intervention; and ii) unable to speak and understand English.

**Table 1 Tab1:** Walking intervention for people with recurrent or metastatic cancer: definitions of recurrent or metastatic disease

Primary tumor	Definition
Breast	Metastatic disease - stage 4, for example, visceral, bone, soft tissue, and so on.
	Not local recurrence
Colorectal	Metastatic - stage 4 - M1
Gynecological	Ovary - symptomatic stage 3/4/recurrence
	Cervix - stage 3/4
	Endometrial - stage 3/4
	Vulva - stage 3/4
Hematological	Lymphoma (high and low grade) within first 6 months of relapse, myeloma
Head and neck	Metastatic disease, recurrence
Melanoma	Stage 3/4
Prostate	Distant metastatic disease or bone metastases (T3, N1, M1)
Upper gastrointestinal	Stage 3/4, oesophago-gastric

Figure 1 shows the flow of participants through the study. Participants will be screened for eligibility by their health-care professional (that is, nurses or doctors) as they visit clinics or via hospital records. Health-care professionals or researchers will describe the study to those identified during a clinic attendance and where appropriate provide a study information pack comprising an invitation letter, information sheet, permission to contact form, a unique study identification number, and postage paid envelope. Those identified via hospital records will be sent the study information pack by post by their health-care professionals. Health-care professionals/researchers will record reasons for ineligibility and reasons for declining participation.

**Figure 1 Fig1:**
[figure not shown]
Walking intervention for people with recurrent or metastatic cancer: flowchart of study protocol.

Patients who are interested in participating in the study will be asked to send their permission to contact form directly to the study researcher, giving consent for the researcher to make telephone contact to describe the study further, assess their willingness to participate, and check whether they can walk for a minimum of 30 min. Those who can, and are still interested in the study, will be sent a consent form, general practitioner (GP) form (to ascertain the details of their family doctor and permission for the researchers to write to inform their GP of their participation in the study), and a baseline questionnaire (T0). Possible outcomes are (1) eligible and willing to participate, (2) eligible and unwilling to participate, and (3) ineligible. Again, wherever possible, reasons for declining participation and ineligibility will be recorded.

### The intervention

The intervention comprises a brief (approximately 10-min) telephone or face-to-face session, based on the UK’s National Institute for Health and Clinical Excellence (NICE) guidance on promoting physical activity in primary care [13]. The study will utilize the preexisting Walking for Health program, a network of UK-wide, freely available walking groups provided by MacMillan Cancer Support and The Ramblers [15]. Participants in the intervention group will be asked to participate in at least one Walking for Health group activity per week and undertake walking for at least 30 min on alternate days over 3 months, either independently or with Walking for Health groups. Walking for Health’s volunteers lead more than 3,000 short walks (lasting approximately 30 min to 1 h) throughout the UK every week. The researcher will assess the patient’s readiness to adhere to the walking intervention and, using motivational interviewing techniques, stimulate their use of study materials as a means to increase physical activity. Increasingly used in health-care settings, motivational interviewing is a patient-centered, counseling style that augments an individual’s motivation to change behavior and move toward a specific goal [16]. It explores the person’s own reasons for change and focuses on their strengths, not just the obstacles and weaknesses associated with change [13,16]. Study materials will be provided in print and online formats to reinforce the intervention. Information on local Walking for Health groups will be provided, including details of the seven Walking for Health coordinators in South East London and how to find out about walks elsewhere. The intervention will be delivered by researchers trained in motivational interviewing. An expert in motivational interviewing will provide supervision to the researchers during this process to ensure adherence to operational procedures and the principles of motivational interviewing. Using random selection, intervention sessions will, with consent, be audio recorded to ensure fidelity to the intervention manual.

### Comparator group

Participants in the comparator group will be asked to continue their activities as usual during the study (standard care).

### Assessments

Participants will complete postal questionnaires at baseline (T0) and at 6 (T1), 12 (T2), and 24 (T3) weeks following recruitment to the study. Two postal reminders will be sent to non-responders. Table 2 provides an overview of the questionnaires that will be completed at each assessment with a rationale for their use. Additionally, those in the intervention group will be asked to record their Walking for Health participation - including date and location of walks attended - on a simple form. Semi-structured telephone interviews will be conducted with ten participants (five per study group) to assess the acceptability of the intervention, randomization, and evaluation of the study methods. At the end of the intervention, a maximum of ten stakeholders (that is, community group coordinators/walk leaders, clinical nurse specialists, research nurses and hospital doctors) will be interviewed by the study researchers (JH, VT) to explore the acceptability of the walking intervention from a professional perspective.

**Table 2 Tab2:** Walking intervention for people with recurrent or metastatic cancer: questionnaire measures by assessment point

Measures included in the study questionnaire	Assessment point			
*Description*	T0 (Baseline)	T1 (6 weeks)^1^	T2 (12 weeks)^1^	T3 (24 weeks)^1^
* Functional assessment of cancer therapy- general* (*FACT-G*) [18]	✓	✓	✓	✓
• *Assesses emotional and physical quality of life in the past 7 days*				
* Depression, anxiety, stress scales* - *21* (*DASS-21*) [19]	✓	✓	✓	✓
• Assesses the frequency and severity of symptoms over the past 7 days				
* General practice physical activity questionnaire* (*GPPAQ*) [20]	✓	✓	✓	✓
• *Assesses physical activity levels (classified as active, moderately active, moderately inactive, inactive) in the past 7 days*				
* Scottish physical activity questionnaire* (*SPAQ*) [21]	✓	✓	✓	✓
• Captures 7-day recall of all leisure and occupational physical activity				
* Spinal cord injury exercise self-efficacy scale* (*ESES*) [22]	✓	✓	✓	✓
• Assesses current exercise self-efficacy				
* Brief fatigue inventory* (*BFI*) [23]	✓	✓	✓	✓
• Assesses severity of fatigue and any impact on functioning in the previous 24 hours				
* Eastern Cooperative Oncology Group* (*ECOG*) [24]	✓	✓	✓	✓
• Measures current performance status, how disease is progressing and affects daily living activities				
* Motivational ruler* [25]	✓	✓	✓	✓
• Includes two visual 100 mm visual analog scales to measure current importance and confidence in walking				
* Patient reported demographics and clinical history*	✓			
• Study specific measure includes sex, age, marital status, education, long-standing health conditions etc.				
* Adverse outcomes and events* (*intervention only*)		✓	✓	
* End of study questionnaire*				✓
• Effects on quality of life (intervention only); usefulness of information; achievement of physical activity goals; satisfaction with study/intervention; free text comments about the study				

^1^Randomization occurs after the baseline questionnaire has been returned. Therefore, follow-up questionnaire timings are as follows: *control group* - from the date of the post-randomization telephone call (for example, informing them they are in the control); *intervention group* - from the date of the motivational interview telephone call.

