### Sample size

For the feasibility trial, we aim to consecutively recruit a minimum of 30 patients with recurrent or metastatic cancer to both the control and intervention groups (60 patients in total). A sample size of 30 per arm will be sufficient to estimate the standard deviation of our QoL outcomes and allow estimation of the true treatment difference. The latter is needed to perform a power calculation for the main study. A definitive sample size of a large-scale RCT will be determined from the results of this trial.

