### Serious adverse events reporting and monitoring

It is not anticipated that there will be any risk to participants. With permission, the researchers will write to all participants GPs to inform them of their participation on the study. Data on unexpected and serious adverse events will be collected at assessments T1 and T2. Any serious adverse events deemed to be related to the intervention or due to participation in the study will be reported to the chief investigator within 24 h of the team learning of its occurrence.

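### Table 2 asks about adverse events in the intervention arm only, while the safety section names no arm; as tabulated, no randomised comparison of events is possible

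*Protocol article*

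**What the plan says.** All references are to the protocol article.

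- **Assessments, Table 2.** The adverse-event row is labelled "Adverse outcomes and events* (*intervention only". It is ticked at T1 (6 weeks) and T2 (12 weeks), and not at T0 or T3.
- **Serious adverse events reporting and monitoring.** "Data on unexpected and serious adverse events will be collected at assessments T1 and T2". No arm is named. On expedited reporting: "Any serious adverse events deemed to be related to the intervention or due to participation in the study will be reported to the chief investigator". The time limit for this is 24 hours, counted from when the team becomes aware of the event.
- **Assessments, text.** The questionnaire schedule covers everyone: "Participants will complete postal questionnaires at baseline (T0) and at 6 (T1), 12 (T2), and 24 (T3) weeks following recruitment to the study". The other repeated measures in Table 2 carry no arm restriction.
- **Pedometers.** A random half of each arm receives a pedometer, and the section accepts that wearing one may itself increase walking in either arm.
- **Sample size.** The target is "a minimum of 30 patients with recurrent or metastatic cancer to both the control and intervention groups (60 patients in total").

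**The concern.** The Background describes a population with pain, fatigue, appetite loss and psychological disorders. Adverse events are therefore to be expected whether or not a patient is asked to walk. A count from the walking arm alone mixes events due to walking with events due to the disease and its treatment, and the control arm is what would separate them.

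Two features of the plan make the restriction harder to defend. Pedometer-wearing controls receive something the protocol thinks may increase walking. The expedited-reporting rule also covers events due to taking part in the study, which can include controls, yet Table 2 gives controls no item on which to report them.

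A primary outcome is whether a full trial is warranted and feasible. The protocol does not say that safety enters that decision, but it is reasonable to expect that it will. As tabulated, the study would give no comparative information on harm and would not test whether collecting such information in both arms works.

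**Working it through.** **1. Figures to reproduce.** The documents state no adverse-event rate and no precision target for harms. The sample size has no power calculation behind it. The only arithmetic to check is 2 × 30 = 60, which agrees.

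**2. The two places side by side.**

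| | Table 2 row | Safety section |
|---|---|---|
| Events | Adverse outcomes and events | Unexpected and serious adverse events |
| Times | T1, T2 | T1, T2 |
| Arm | Intervention only | Not stated |

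The matching times suggest a single collection, in which case the Table 2 restriction applies to all of it. The alternative is that serious events are meant to be collected in both arms. Table 2 is then wrong or incomplete for that class, and other events remain one-arm. The text does not settle which is meant.

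**3. What one arm can show.** Write the intervention-arm event proportion as r = b + e, with b the background rate and e the excess due to walking. One-arm data estimate r only. An observed 6 of 30 (r = 20%) fits b = 20%, e = 0 as well as b = 10%, e = 10 points. More patients would sharpen r but would not separate b from e.

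Exact (Clopper-Pearson) 95% intervals for r with n = 30:

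| Patients with an event | 95% interval |
|---|---|
| 0 | 0 to 11.6% |
| 3 | 2.1 to 26.5% |
| 6 | 7.7 to 38.6% |
| 9 | 14.7 to 49.4% |

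**4. What two arms would show.** Inputs are 30 per arm (Sample size section), no losses (assumption), and a common event rate p (assumption, varied because the documents give none). The 95% half-width of the risk difference is 1.96 × √(2p(1 − p)/30).

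| Assumed p | Calculation | Half-width (points) | Power for a 20-point excess, two-sided 5% |
|---|---|---|---|
| 10% | 1.96 × √(0.18/30) = 0.152 | 15 | 49% |
| 20% | 1.96 × √(0.32/30) = 0.202 | 20 | 39% |
| 30% | 1.96 × √(0.42/30) = 0.232 | 23 | 35% |
| 40% | 1.96 × √(0.48/30) = 0.248 | 25 | 34% |

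The power column takes p as the control rate and p + 20 points as the intervention rate.

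**5. Timing.** Recruitment closed on 30 November 2014. Twelve weeks later is 22 February 2015, and the article appeared on 12 March 2015. Under the Table 2 footnote the clock starts at a telephone call after randomisation, so some lag is possible. Even so, most T1 and T2 questionnaires would have gone out by publication.

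**The case against.** The strongest reply is that this is a 60-patient feasibility study. Its objectives and secondary outcomes list no comparative safety estimate, and the comparison forgone would be imprecise. That stands, and it limits the severity. It does not justify leaving out the control arm: imprecise estimates are the normal product of a feasibility trial, whereas the present table yields no comparison at all. Quality of life, fatigue, performance status and reasons for attrition carry no arm restriction and give indirect signs of deterioration, but they do not replace event counts. Collecting events in both arms would not remove relatedness judgement either; it would add a comparison that does not depend on it.

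A reader might go further in several directions that the documents do not support.

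- **That controls certainly yield no serious-event data.** The safety section is silent on the arm. This is unclear rather than established.
- **That stopping at week 12 is what prevents separation from background.** Participants are asked to "undertake walking for at least 30 min on alternate days over 3 months", so T2 falls at about the end of the prescribed walking. Adding T3 in the intervention arm alone would separate nothing. The cut-off misses only later events, including any from walking that participants continue.
- **That walking is made to look harmful by construction.** No between-arm comparison of events is planned, and a one-arm listing does not report the control count as zero. The data are uninterpretable as a contrast, not tilted.
- **That the safety section contradicts the eligibility criteria.** The expectation "It is not anticipated that there will be any risk to participants" stands beside an exclusion for "having bone metastases which the responsible health-care professional considers a contraindication to participating in the walking intervention". The exclusion removes patients judged unsuitable for walking and so can support the expectation for those enrolled.
- **That the 24-hour rule is defective or that a contact route between questionnaires is missing.** The clock runs from the team's awareness and is not inconsistent. Contact routes commonly sit in the full protocol or the information sheet, which are not shown.

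**Conclusion.** The point holds for the arm restriction and for the mismatch between Table 2 and the safety section. As Table 2 stands, a between-arm difference in adverse events cannot be estimated, and attribution of intervention-arm events rests on judgement made with the arm known. Asking both arms would give a comparison protected by randomisation, with a 95% half-width of roughly 15 to 25 points.

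That range assumes event rates of 10% to 40%, 30 respondents per arm, and the same completeness of reporting in both arms. Losses would widen it. Severity is moderate: this is a flaw in a stated design choice that matters for what the study can pass on to a main trial, but it does not undermine the feasibility and acceptability outcomes.

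**What to change.** 1. In Table 2, remove the restriction from the adverse-event row and ask the same items in both arms at T1 and T2. T3 is optional, to cover walking continued after the intervention.
2. In the section on serious adverse events, state that collection is in both groups, so that it agrees with the table.
3. Report, by randomised arm, the number of patients with an event and the risk difference with its 95% interval. Label this descriptive.
4. Report one-arm counts already collected as non-comparative.

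The cost is a slightly longer control-arm questionnaire and an amendment to the approved study design. With recruitment closed, the change reaches only questionnaires not yet sent, probably mainly T3, and would largely not recover the comparison during the intervention period. Its main value is therefore in the main-trial design.
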